### Study design

An effectiveness-implementation type 2 design will be used [33], since this study will assess both the effectiveness of the intervention and the implementation process in the same degree, as co-primary aims [34]. The empirical study will take a stepped wedge (SW) cluster randomized controlled trial design; this design implies that every participant starts the trial in the control phase (no exposure to the intervention), and then undertakes the intervention in a staggered and sequential way. Once it is completed (8 weeks), the maintenance phase takes place, during which the participant can continue to use the program at will, but without supervision. There will be three possible sequences (see Fig. 1), and each of the participating centers will be randomly assigned to one of them. The participants from each site will all follow the same sequence.

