**Fig. 1 Fig1:**
[figure not shown]
The three possible sequences of the study phases. *Note:* A = Control phase; B = Intervention phase; C = Maintenance phase. Each cell represents a period of 8 weeks

SW designs are particularly recommended when the intervention being tested has strong evidence of positive effects or is very unlikely to cause harm [35], which is the case of our study. The present work is considered a closed cohort study, since all the study participants will start at the same time and will be evaluated at different time-points to be defined beforehand; the inclusion of new participants will not be allowed once the trial has commenced.

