Clear indications will be given on how to use the platform in the welcome module (see Table 1). Participants will be assessed for all the study variables every 8 weeks; the usability measure (System Usability Scale, SUS) [38] will be completed after finishing module 1 and module 4. The research team will record the usage that each participant makes of the platform: the number of times it was accessed, modules completed, and number of tasks delivered. Two external professionals, one in each province and unrelated to the research group, will be in charge of monitoring the intervention, providing feedback to the participants, and making weekly contact with participants via their preferred means (telephone call, text message, or email); this contact will be used to motivate participants to complete the intervention. Both professionals will previously have been trained in the contents and procedures of the MINDxYOU program by the research team. Once the intervention is complete, focus groups will be held in the provinces of Zaragoza and Malaga to qualitatively assess the acceptance and suitability of the intervention, and interviews will be conducted with managers and directors from each site to evaluate different aspects regarding implementation of the program.

**Table 1 Tab1:** Brief outline of the MINDxYOU program

Module	Main contents	Main practices
0. Welcome module	This module will introduce participants to the platform and present the main aims of the intervention	Participants will be given the opportunity to share their feelings and needs, and will receive feedback from the research team
1. Mindfulness	The concept of mindfulness will be explained, together with its applications for stress reduction and the promotion of good mental health	Body scan, sitting meditation, three-minute breathing meditation
2. Compassion	The concept of compassion will be explained, together with its applications for stress reduction and the promotion of good mental health	Compassionate breath meditation, compassionate body scan, safe place meditation
3. Acceptance	The concept of acceptance will be explained, together with its applications for stress reduction and the promotion of good mental health	Meditation focused on acceptance, identification of personal values

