### Data analysis

#### Effectiveness analysis

Both intention-to-treat analysis and per-protocol analyses (i.e., those participants who complete at least 4 of the 5 modules of the intervention) will be performed. The analyses will include the description and elementary head-to-head comparisons between both phases (i.e., control vs. intervention). Specifically, the variables for each of the phases will be described by using descriptive statistics (means and 95% confidence intervals in the case of quantitative variables with normal distribution, medians, and interquartile range in the case of quantitative variables with non-normal distribution). To confirm the main hypothesis, all of the effectiveness variables (i.e., PSS and secondary outcomes) will be compared between the intervention and control phases. A multilevel regression analysis will be performed including the cluster as a random effect, and multivariate multilevel regression analysis will be performed to adjust for possible confounders. The magnitude of the effect of the improvement and the Number Needed to Treat (NNT) will also be reported, using the cut-off points already established in the primary outcome as criteria for considering whether a participant is a responder.

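### The confirmatory model names only the cluster as a random effect, although the same participants supply repeated PSS scores in both phases; fitted as written, its standard errors are too large

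*Protocol article*

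**What the plan says.** All statements are in the protocol article.

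- **Study design:** "There will be three possible sequences (see Fig. 1), and each of the participating centers will be randomly assigned to one of them". Everyone begins unexposed and later receives the intervention. The section adds: "The present work is considered a closed cohort study, since all the study participants will start at the same time".
- **Procedure:** "Participants will be assessed for all the study variables every 8 weeks".
- **Effectiveness analysis:** for the main hypothesis, "all of the effectiveness variables (i.e., PSS and secondary outcomes) will be compared between the intervention and control phases". The model is given as a multilevel regression "including the cluster as a random effect". A second, multivariate model adds adjustment for confounders and no further level.
- **Sample size:** the only correlation used is the intra-class correlation of 0.04.

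No participant random effect, repeated-measures covariance or robust variance is stated anywhere in the article.

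**The concern.** Each participant contributes scores to both sides of the comparison. Scores from one person are correlated, and much of that correlation cancels when the person's control and intervention scores are compared. A model with a cluster effect alone treats two scores from one person as no more alike than scores from two colleagues at the same center. It therefore puts stable differences between people into the residual, and they inflate the standard error of a contrast that lies largely within people.

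The confidence intervals and p-values for the PSS, and for the secondary outcomes analysed the same way, would be miscalibrated. The practical risk is a missed effect. The Background section says that most comparable online programs achieved only small effects, which is where lost precision matters most.

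**Working it through.** **The article's own figures.** With d = 0.50, two-sided 5% and 80% power, n per arm = 2(1.96 + 0.8416)²/0.50² = 62.8, so 63, and 126 in total, as stated. The last steps also reproduce: 24/0.8 = 30 and 30 × 6 = 180. The step between does not: 126 × 0.96/(6 − 126 × 0.04) = 126 per cluster, not 24. That is a separate matter. I take the stated 24 as the analysed cluster size.

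**Inputs from the article.** 6 clusters, 24 people each, ICC 0.04, three sequences.

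**Assumptions.**
- Two centers per sequence, and layouts ABCC/AABC/AAAB or ABCCC/AABCC/AAABC. The maintenance phase C is either left out or counted as treated.
- Period effects are in the model, and total variance is 1.
- Cluster autocorrelation c (how far a center's deviation persists between periods) is 0.8 to 1.
- Individual autocorrelation a (the same for a person's deviation from the center) is 0.3 to 0.7. The article gives no 8-week value.

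**Variance of the center-by-period means.** J is the all-ones matrix and I the identity. Note that 0.96/24 = 0.04.
- Cluster-only model: W = 0.04 J + 0.04 I
- Closed cohort: V = 0.04(c + a) J + 0.04(2 − c − a) I

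The I part drives a within-center contrast. With c = 1 and a = 0.5 it is 0.04 in the model but 0.02 in truth.

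**Standard errors.** With A = ΣX′W⁻¹X over clusters:
- reported variance: A⁻¹
- true variance of the same estimator: A⁻¹(ΣX′W⁻¹VW⁻¹X)A⁻¹
- variance with the correct covariance: (ΣX′V⁻¹X)⁻¹

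Actual type I error is 2Φ(−1.96 × reported/true). Power with the cluster-only model is Φ[(d − 1.96 × reported)/true]. With the correct covariance it is Φ(d/SE − 1.96).

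| Layout | c / a | Reported SE | True SE | SE, correct covariance | Reported/true | Type I error | Power at d = 0.3: cluster-only / correct |
|---|---|---|---|---|---|---|---|
| 4 periods, A vs B | 0.8 / 0.3 | 0.1562 | 0.1503 | 0.1501 | 1.04 | 4.2% | 48% / 52% |
| 4 periods, A vs B | 0.8 / 0.7 | 0.1562 | 0.1239 | 0.1170 | 1.26 | 1.3% | 48% / 73% |
| 4 periods, A vs B | 1 / 0.3 | 0.1562 | 0.1377 | 0.1355 | 1.13 | 2.6% | 48% / 60% |
| 4 periods, A vs B | 1 / 0.7 | 0.1562 | 0.1082 | 0.0924 | 1.44 | 0.5% | 48% / 90% |
| 5 periods, C as treated | 0.8 / 0.3 | 0.1414 | 0.1350 | 0.1349 | 1.05 | 4.0% | 57% / 60% |
| 5 periods, C as treated | 1 / 0.7 | 0.1414 | 0.0869 | 0.0796 | 1.63 | 0.1% | 60% / 96% |

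The 48% is easy to see: significance needs an estimate above 1.96 × 0.1562 = 0.306, just over the assumed 0.3. At d = 0.50, cluster-only power ranges from 90% to 99% over all layouts and correlations.

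**Simulation check** (150 mixed-model fits per setting, c = 1). With a total within-person correlation of 0.6, the mean reported SE was 0.155 and the empirical SD 0.115; the exact calculation gives 0.156 and 0.118. With 0.77, they were 0.157 and 0.101; the exact calculation gives 0.156 and 0.103. Rejection rates under no effect were 1.3% and 0.7%.

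**The case against.** **The wording does not exclude a participant level.** To include the cluster is not to include it alone, and the unseen SAP may add the level. So a reader should not infer that the plan declares repeated scores independent; it does not say so. What stands is that the article states the random part of its confirmatory model and names one level, and that level does not match a closed cohort.

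**Period effects are not named either, yet the figures assume them.** True, but the misstatement does not depend on them. Without them, at c = 1, the ratio is 1.09 to 1.99 for total within-person correlations of 0.2 to 0.77. The power loss at d = 0.3 does depend on them: without period terms, cluster-only power is 86% or more.

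**The harm is limited.** A reader might infer that false positives are inflated, or that the trial is underpowered for its target. Neither is supported: the error was conservative in every case run, and power at d = 0.50 stays at about 90% or more. The value 0.3 is illustrative and is not the article's.

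**The correlation is unknown.** The test–retest value of 0.77 under Primary outcome is given without an interval and cannot be read as an 8-week correlation. At the mild end (c = 0.8, a = 0.3) the misstatement is only about 4%.

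**Conclusion.** The point holds as a badly fixed analysis choice of moderate consequence. As written, the primary model overstates the standard error of the phase contrast by about 4% to 63% under the assumptions above. Tests are too conservative and intervals too wide. The planned effect would still be detected, but a smaller real effect could be missed.

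The size rests on assumed layouts, assumed autocorrelations and normal approximations. With 6 clusters the absolute power figures are optimistic, so the ratios are the firmer result. Where c is below 1, the correct covariance also contains a cluster-by-period component. At c = 1 a participant effect alone supplies it, and power at d = 0.3 is then 60–96%, against 48–60% for the cluster-only model.

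**What to change.** In Effectiveness analysis, state that the primary model has a random effect for participant nested in cluster in addition to the random effect for cluster, and that the same structure applies to the secondary outcomes. Do this before the outcome data are analysed, so that the choice cannot appear to depend on the results.

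Two refinements are optional and can be left to the SAP: a cluster-by-period random effect, in case center means drift between periods, and a small-sample degrees-of-freedom correction for 6 clusters.

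The cost is one sentence, with no change to recruitment, assessments or conduct. The small downside is extra variance components to estimate. The participant component is informed by 6 × 24 = 144 people, whereas a cluster-by-period component would rest on few clusters.

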#### Economic evaluation

The economic evaluation will be carried out following the recommendations of the Spanish guidelines for the economic evaluation of health technologies [74]. A societal perspective will be adopted, considering both direct and indirect costs. The cost-utility analyses will consider the effect of the intervention on the QALYs, and the results will be expressed in terms of the incremental cost-utility ratio (ICUR), calculated by dividing the difference in total costs between the intervention phase and the control phase by the difference in QALYs between both phases. A cost-effectiveness analysis will be also conducted, in this case considering the effect of the intervention on perceived stress (PSS). These results will be expressed in terms of the incremental cost-effectiveness ratio (ICER), calculated by dividing the difference in total costs between the treatment phase and the control phase by the difference in PSS scores between both phases.

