#### Cost-utility variables

The five-level version of the *EuroQol five-dimensional classification system* (EQ-5D) [59] is a widely used health-related quality of life measure. First, participants are asked to report the severity (1 = no problems, 2 = mild, 3 = moderate, 4 = severe, 5 = extreme) of the problems they may present on the day of reporting with regard to each of the following five domains: mobility, self-care, usual activities, pain, and anxiety/depression. The combination of the answers given to these domains results in 3,125 different health states. The utility scores are obtained from the EQ-5D classification system and are used to rate patients’ health-related quality of life, which normally range between 0 (although it is possible to present negative scores) and 1 (i.e., “perfect health”). These utility values will be calculated using the Spanish tariffs of EQ-5D-5L [60]. EQ-5D utility values will be used to estimate quality-adjusted life-years (QALYs), a common measure to assess the outcomes associated with different treatments, both in terms of patients’ quality of life and survival [61]. EQ-5D also asks participants to use a visual analog scale (EQ-VAS) to record their current overall health status, ranging between 0 (worst imaginable health) and 100 (best imaginable health).

The *Client Service Receipt Inventory* (CSRI) [62] is one of the most widely used resource-use measurement tools; it describes and measures service utilization patterns as a basis for estimating associated costs across healthcare, social care, and community settings. In the present study, the Spanish version [63] will be used to collect retrospective data (last 2 months) on medication and service use. For medication intake, patients will be asked to bring their daily medication prescriptions, and the following information will be recorded: drug name, dosage, total number of prescription days, and daily dosage consumed. With regard to service use, patients will be asked about total visits to emergency departments, total days of general inpatient hospital admissions, number of diagnostic tests administered, and total visits to primary care physician, nurse, social worker, psychologist, psychiatrist, group psychotherapy, and other community healthcare professionals, specifying in each case if these services were provided by the public or by the private sector.

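### The ICUR and the ICER's cost numerator have no common time base, although control time differs by sequence and exceeds the 8-week intervention phase in at least two of three

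*Protocol article*

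**What the plan says.** The Economic evaluation section of the protocol article gives two explicit formulas. The ICUR comes from "dividing the difference in total costs between the intervention phase and the control phase by the difference in QALYs" between the two phases. The ICER comes from "dividing the difference in total costs between the treatment phase and the control phase by the difference in PSS scores between both phases". Just before these, the section says: "A societal perspective will be adopted, considering both direct and indirect costs". It does not state the length of time over which costs or QALYs are counted, or whether the phases are put on the same scale.

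Under Study design, every participant begins in control and "then undertakes the intervention in a staggered and sequential way". There are three sequences, allocated by centre. On the intervention the text reads "Once it is completed (8 weeks), the maintenance phase takes place". The legend of Fig. 1 makes each cell 8 weeks, and the text after it says that all participants start together.

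On data collection, the Assessment plan has assessments every 8 weeks after baseline. Under Cost-utility variables, EQ-5D utilities are turned into QALYs, and the CSRI "will be used to collect retrospective data (last 2 months) on medication and service use".

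**The concern.** A cost total and a QALY total both grow with the time over which they are counted. In a parallel-group trial with equal follow-up this does no harm. In a stepped wedge with a common start, staggered crossover means that time in control differs between sequences, and in most of them it is longer than the intervention phase. A difference between phase totals then mixes the effect of the programme with the extra weeks spent in control.

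The protocol intends to conclude whether the programme is cost-effective (Discussion). If the formulas were applied to phase totals, that conclusion could reverse in direction for reasons unrelated to the programme.

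**Working it through.** The protocol reports no economic figure to reproduce, so this is an illustration of what the stated formulas do.

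**Phase lengths.** Intervention: 8 weeks (Study design). Control: everyone starts at once and in control, there are three staggered sequences, and cells are 8 weeks. Three distinct crossover times in whole cells, each after at least one control cell, cannot be shorter than 1, 2 and 3 cells, that is 8, 16 and 24 weeks. This is an inference, since Fig. 1 is not available here. With balanced sequences (assumed), mean control time is (8 + 16 + 24)/3 = 16 weeks.

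**Formulas on phase totals.** Let T be control weeks, u the control utility, g the true utility gain held for the full 8 weeks, c the background cost per 8 weeks and d the true extra cost per 8 weeks. None of u, g, c and d is in the protocol; all are assumed.

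- QALY difference = [(u + g)·8 − u·T]/52 = g·8/52 − u·(T − 8)/52. The first term is effect, the second is phase length.
- Cost difference = (c + d) − c·T/8 = d − c·(T/8 − 1).

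**Size of the QALY length term at T = 16.**

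- u = 0.70: 0.70 × 8/52 = 0.108, so −0.108
- u = 0.85: 0.85 × 8/52 = 0.131, so −0.131
- u = 0.95: 0.95 × 8/52 = 0.146, so −0.146

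**Size of the effect term.**

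- g = 0.02: 0.02 × 8/52 = +0.003
- g = 0.05: 0.05 × 8/52 = +0.008

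At u = 0.85 the length term is 0.85/0.05 = 17 to 0.85/0.02 = 42.5 times the effect term.

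**Worked example** with u = 0.85, g = 0.03, c = 300, d = 100 (monetary units) and a 3-point PSS reduction:

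| Control time | QALY difference | Cost difference | ICUR | Cost per PSS point reduced |
|---|---|---|---|---|
| 8 weeks | (7.04 − 6.80)/52 = +0.0046 | 400 − 300 = +100 | about 21,700 | +33 |
| 16 weeks | (7.04 − 13.60)/52 = −0.126 | 400 − 600 = −200 | about 1,590 | −67 |
| 24 weeks | (7.04 − 20.40)/52 = −0.257 | 400 − 900 = −500 | about 1,950 | −167 |

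The first row is also the result per 8-week period for every sequence. In the other two rows the same programme appears to lose QALYs and save money. The ICUR stays positive because both of its parts have changed sign. In the ICER only the numerator moves; a PSS score does not accumulate.

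The apparent saving needs c·(T/8 − 1) to exceed d. With c = 100 and d = 200 at 16 weeks the cost difference is 200 − 100 = +100, so there is no saving, although the cost is still understated by 100 and the QALY loss remains.

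**The case against.** The strongest reply is that total costs may simply mean direct plus indirect costs, since the sentence on the societal perspective comes just before. Assessments are 8-weekly and cost recall is about one cell, so a per-period contrast is possible with the planned data, and a competent analyst might make it without being told. This is also a condensed article that follows national guidelines and may have a fuller plan behind it. Part of this stands: the distortion follows from applying the formulas to phase totals, and it is not certain to occur. But the reading of total costs does not help the QALY denominator, because a QALY difference between phases of unequal length contains a length term under any reading of total. Nor does any other section supply a per-period rule. The formula is stated and does not fit the design, which is different from detail left to another document.

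Stronger readings that a reader might infer are not supported:

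- **That both ratios mostly measure phase length in all sequences.** The ICER's PSS denominator is unaffected, and a sequence with 8 weeks of control has no length artefact in either ratio.
- **That control is stated to last 8, 16 or 24 weeks.** The text does not give these values.
- **That the ICER has the wrong sign.** The section divides "by the difference in PSS scores between both phases" and fixes no direction of subtraction. This is a labelling matter.
- **That the 2-month CSRI recall biases the comparison.** Two months against 56 days is about 61/56 = 1.09, the same scale factor in both phases, with about 5 days of carry-over. It is too small to pursue.

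**Conclusion.** The point holds as a defect in a stated rule. The ICUR, and the cost numerator of the ICER, are defined on phases whose lengths must differ by design, with no common time base. On phase totals and a mean control time of 16 weeks, length contributes −0.108 to −0.146 QALY, against +0.003 to +0.008 from a plausible effect. The sign of the incremental QALY would therefore be set by the schedule and not by the programme.

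The result rests on the inferred cell counts, balanced sequences, constant utility within a phase, and the assumed ranges for utility (0.70 to 0.95) and gain (0.02 to 0.05). No choice within those ranges changes the direction at 16 weeks.

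Severity is moderate. Study aims lists the economic evaluation among the secondary aims, and the PSS effectiveness result and the co-primary implementation aim are untouched.

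**What to change.** In the Economic evaluation section:

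1. Define costs and QALYs per participant per 8-week period.
2. Estimate incremental cost and incremental QALY per 8 weeks in a multilevel model with cluster and participant effects and a term for calendar period. The period term has to be added explicitly: the Effectiveness analysis section names cluster as a random effect and adjustment for possible confounders, but no period term. Rescaling to 8 weeks removes the length artefact; the period term is needed because control time falls earlier than intervention time.
3. Form the ICUR and ICER from these increments.
4. Express the ICER as cost per PSS point reduced, so that its sign cannot be misread.
5. Say whether the maintenance periods enter this model.

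The cost is a few sentences of analysis text. The 8-weekly assessments already supply the data, so no new collection, visit or participant is needed.
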